### Ethical considerations

The MDP301 trial is being carried out in accordance with international good clinical practice (ICH GCP) guidelines. Ethical permission to carry out the trial was given by local university or national research ethics committees in South Africa, Tanzania, Uganda and Zambia. Two ethics committees in the UK reviewed the protocol. The protocol was also reviewed by the national regulatory authorities in each participating country, as well as the Food and Drug Administration in the US where gel was manufactured. The trial commenced in October 2005 and completed enrolment in August 2008. Four versions of the protocol were implemented during this period on receipt of the necessary approvals.

### Informed consent

Informed consent was obtained through a two-stage procedure. Women were initially requested to give consent for screening and then subsequently, if they were eligible, for enrolment and randomisation. An interval of one to six weeks between the screening and enrolment visits allowed sufficient time for women to consider carefully whether they wished to take part. On both occasions, information was given to women about microbicides, the risks and benefits of taking part, confidentiality and their right to withdraw at any time, as well as details of the trial procedures. Information was provided during one-to-one interviews with the help of written materials and visual aids, and women were given the opportunity to raise any questions or concerns. Volunteers were next asked three questions that could not be answered yes or no to ascertain that they understood (a) that gel might not protect them from HIV, (b) that condoms do prevent HIV and (c) that they would have to stop using the gel if they became pregnant. Following this procedure, if women agreed to take part they were asked to indicate their consent by signature or thumbprint. If the woman was illiterate, an impartial witness of her choice was present to witness the discussion and her thumbprint consent.

Key points addressed during the informed consent procedure at enrolment were: (a) that the trial is being conducted to find out whether the gels will prevent HIV infection; (b) that there is a one in three chance that participants will receive the placebo gel and that no-one, including the staff, will know which product she is using; (c) that women are asked to use the gel during all sex acts and, because it is not known if the gels are active, that it is best if condoms are also used whenever possible; (d) that women will have to be withdrawn from gel if they become pregnant; (e) that symptoms such as genital irritation, unexpected bleeding, sores and ulcers should be reported to the study team regardless of whether the participant thinks they are related to product use; and (f) that they are asked to answer questions, especially those regarding gel use and sexual practices, as accurately as possible.

At specific visits during follow-up each participant's comprehension of the following is reviewed: a) that no-one knows whether any of the study products will protect against HIV or STI infections and so it is best to use condoms with gel; b) that they should contact the study staff before their next appointment if they have a problem such as bleeding or suspect that they might be pregnant; c) that they need to try to answer the questions about gel use accurately; d) that they are free to withdraw or stop using gel at any time.

### Standard of care

At the 12, 24, 40 and 52 week clinic visits, women are provided with HIV testing and counselling with promotion of safer sex practices, provision of free condoms, and diagnosis and treatment of sexually transmitted diseases. Women are advised to use a reliable method of contraception during the trial and several are available through the research clinics. A pregnancy test is carried out at every scheduled visit to the clinic. Women who become pregnant are withdrawn from study gel but asked to continue to attend their clinical follow-up visits, and will be followed up to record the outcome of pregnancy and included in a secondary MITT analysis (see below).

Women found to be HIV-positive at screening or who become HIV seropositive during follow-up are referred to local services for HIV treatment and care according to procedures developed at each study site.

### Trial oversight

MDP301 has an Independent Data Monitoring Committee (IDMC) which meets every 4-6 months to review the data on adverse events and HIV incidence by study arm and consider any emerging current literature. The IDMC is responsible for advising the Trial Steering Committee (TSC) of any changes that it recommends in the conduct of the study that may be required during the course of the trial. Because of the unique nature of the trial whereby HIV-seroconversion is the primary endpoint for both efficacy and safety the IDMC have had access to unblinded data on seroconversion rates by study arm at all of their meetings. No formal stopping rules were suggested for safety concerns. There was one planned efficacy interim analyses which took place after accumulation of half the expected woman-years, and the IDMC were to advise the TSC to stop the trial early in the event of overwhelming evidence of efficacy (p < 0.001). Adopting this approach allows for (approximate) preservation of the type I error rate at the end of the trial[12,13].

Community mechanisms have been established in each study site to facilitate a two-way flow of information between the study team and study population and to provide a forum where any concerns about the trial can be discussed.

### Sample size

At study onset, the proposed primary endpoint was HIV sero-conversion by the week 40 visit in a participant confirmed to be negative at enrolment. The enrolment target was originally 9673 women, to enable 2055 woman-years per arm to be accumulated by 40 weeks, allowing for 15% loss of woman-years due to withdrawals for pregnancy and loss to follow-up.

As indicated previously we assumed a conservative estimate of HIV incidence in the placebo arm of 4.0 per 100 woman-years. It was considered unrealistic to expect high efficacy against HIV incidence, and 40% was considered to be the highest efficacy likely to be achieved. Thus the power of the study to detect a 40% reduction in incidence in either of the active gel arms, compared with the placebo arm, as significant at the 5% level, would be 82%, increasing to 89% if incidence is 5.0 per 100 woman-years. The study was not powered for a comparison of the two active gel arms.

Following two protocol amendments described later, the primary endpoint was moved to week 52 and the sample size adjusted in order to achieve 80% power at the lower effect size of 35% reduction in HIV incidence. A revised estimate of 2640 woman-years per group is now required in order to achieve this.

Sample size calculations were also carried out for secondary and safety endpoints. Data from feasibility and other studies in the study sites indicated HSV-2 prevalence ranging from 50% to 85%, and HSV-2 incidence of approximately 10 per 100 woman-years. Assuming that 75% of the study population is already infected at enrolment and that HSV-2 incidence is 10 per woman-years then given approximately 1920 evaluable woman-years of observation at 52 weeks, the trial would have 90% power to detect a 50% reduction in HSV-2 incidence or 71% power for a 40% reduction. It is also proposed to compare the prevalence of NG and CT infection at the 24 week clinic visit. Assuming that approximately 7500 women are seen at this visit, there will be 89% power to detect a reduction in prevalence of either infection from 6% to 4%, 94% for a reduction from 3% to 1.5% or 59% power for a reduction from 3% to 2%. Assuming a minimum of 3000 women are enrolled in each study arm, there will be considerable power to detect small increases in rare adverse events, for example 97% power to detect an increase from 1.5% to 3%, or 80% power to detect an increase from 0.5% to 1.2% or 0.1% to 0.5%.

### Modified intention to treat analysis

The primary analysis will be a modified intention to treat (MITT) analysis in which women will be censored if they are withdrawn from gel because they become pregnant, but not if they are withdrawn for other reasons unless they refuse further follow-up. Following, the protocol amendment to allow women to restart gel following a negative pregnancy test, the additional woman-years accrued after re-starting gel will also be included in the MITT analysis.

Intention to treat analysis is usually recommended to preserve the comparability of study arms that is ensured by randomisation and to avoid selective exclusion of data on participants who may respond differently to the intervention from those who remain under follow-up throughout. The justifications for adopting a MITT approach in this trial are that (a) withdrawal for pregnancy is required by the study protocol for safety reasons and does not reflect a participant decision to withdraw which might be related to experience of the gel; (b) pregnancy rates are not expected to be influenced by gel use, so that the comparability of study arms ensured by randomisation should be maintained; and (c) while women are encouraged to use effective methods of contraception, pregnancy rates in all study sites remain substantial so that a classical intention to treat analysis would be expected to considerably under-estimate product efficacy and thus to reduce the power of the study.

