At the time when the N9 results were released (June 2000), five research groups were planning programmes of research to evaluate six candidate microbicides. One of these candidates was PRO 2000/5, a naphthalene sulphonate polymer which disrupts the attachment and fusion steps in HIV infection of target cells. In this paper, we describe the rationale and design of an ongoing multi-centre Phase III trial of PRO 2000/5 which is being carried out by the Microbicides Development Programme. This is the largest Phase III microbicide trial to date, with 9404 enrolments, and is scheduled for completion in August 2009. We also discuss adaptations to the design that have been made during the conduct of the trial.

The main objective of the trial, designated MDP301, is to determine the efficacy and safety of 0.5% and 2% concentrations of PRO 2000/5 gel compared to placebo in preventing vaginally acquired HIV infection.

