### Closure of 2% study arm

Following a review of the data accrued by 15^th ^January 2008, the IDMC recommended that the 2% gel arm should be terminated on the grounds of futility, indicating that continuation of this study arm would be unlikely to demonstrate significant benefit of this concentration of PRO 2000/5. This recommendation was accepted by the TSC, and women remaining on 2% gel at that time were withdrawn from gel, but asked to continue to attend the long clinic visits at weeks 4, 12, 24, 40 and 52.

The closure of the 2% arm provided an opportunity to redirect resources to maximise the precision and power of the trial for the 0.5% gel *vs *placebo comparison. It was decided to continue with the original enrolment targets, but with women randomised in a 1:1 ratio to the 0.5% and placebo arms.

Figure 3 shows the estimated power of the study following the above design changes, with a 52 week primary endpoint and increased enrolment to the 0.5% and placebo arms. It shows that the trial will now have 80% power to detect a lower effect size of 35% assuming a control incidence of 4% (conservative) in the control arm. This increases to 85% and 88% assuming a control incidence of 4.5% and 5% respectively.

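### Under the stated MITT rule, off-gel follow-up after closure of the 2% arm counts as 2% gel time, which would dilute the 2% versus placebo HIV estimate

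*Protocol article*

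**What the plan says.** The section Modified intention to treat analysis sets the censoring rule for the primary analysis. It says that "women will be censored if they are withdrawn from gel because they become pregnant". The part that matters here completes the same sentence and covers every other cause of withdrawal: "but not if they are withdrawn for other reasons unless they refuse further follow-up". The section gives three reasons for censoring at pregnancy: (a) the protocol requires the withdrawal, so it is not the participant's choice; (b) pregnancy rates should not depend on gel; (c) keeping the off-gel time would noticeably understate efficacy.

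The section Closure of 2% study arm reports that "the IDMC recommended that the 2% gel arm should be terminated on the grounds of futility", after a review of data to 15 January 2008. It adds that "women remaining on 2% gel at that time were withdrawn from gel, but asked to continue to attend the long clinic visits", through week 52. Enrolment then continued "with women randomised in a 1:1 ratio to the 0.5% and placebo arms".

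The Background still gives the main objective as "to determine the efficacy and safety of 0.5% and 2% concentrations of PRO 2000/5 gel compared to placebo". The section Primary endpoints makes HIV incidence a primary safety endpoint as well as the efficacy endpoint. The article neither exempts arm closure from the censoring rule nor sets a follow-up cut for the 2% arm.

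**The concern.** Withdrawal because the arm closed is a withdrawal for another reason, so the rule keeps these women in the analysis. Their remaining follow-up is attributed to 2% gel although they have none, while placebo women of the same calendar period continue on gel. The comparison then mixes on-gel and off-gel time in one arm only.

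This conflicts with the plan's own reasoning. Closure meets reason (a), because the trial imposed it, and reason (c), because the time is off gel. Reason (b) concerns balance between arms. Censoring the 2% arm alone would not respect it, but one calendar date applied to both arms would.

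There is a second imbalance. The pregnancy trigger is withdrawal from gel because of pregnancy. A 2% woman already off gel cannot meet it, whereas a placebo woman who becomes pregnant is censored. After closure the two arms are therefore censored by different rules in practice.

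At stake is the final 2% versus placebo estimate. The section Study arms says that local toxicity raising HIV risk had to be considered at the higher concentration, so dilution matters for detecting harm as much as for estimating benefit.

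**Working it through.** **Inputs from the article.** Placebo incidence 4.0 per 100 woman-years; 40% reduction; 5% level (taken as two-sided); 2055 woman-years per arm; stated power 82% (Sample size). "The trial commenced in October 2005 and completed enrolment in August 2008" (Ethical considerations). Data cut for closure 15 January 2008. Endpoint at 40 weeks at first, later 52 weeks.

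**Plan's own figure.** Rate-difference test: z = (0.040 − 0.024) / √[(0.040 + 0.024)/2055] = 0.0160/0.00558 = 2.87. Power = Φ(2.87 − 1.96) = 81.8%, against 82% stated. The log rate ratio method gives 81.0%.

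**Assumptions.** A = months of accrual to gel withdrawal, taken as 24 to 30 and centrally 27.5 (October 2005 to shortly after mid-January 2008). F = follow-up per woman, 9.2 months (40 weeks) or 12 months (52 weeks). No losses, constant incidence, and a rate ratio of 1 once off gel.

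**Off-gel share f of 2% woman-years.**
- Uniform accrual: a fraction F/A of the arm is still in follow-up at closure and loses F/2 months of gel on average, so f = F/(2A). At A = 27.5 and F = 12, f = 12/55 = 21.8%.
- Linearly rising accrual: f = F/A − F²/(3A²). At A = 27.5 and F = 12, f = 0.436 − 0.063 = 37.3%.

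**Dilution.** Measured rate ratio = (1 − f) × RR + f.

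| Accrual to closure | Endpoint | f | True 40% reduction measured as | True RR 1.5 measured as |
|---|---|---|---|---|
| Uniform, 30 months | 40 weeks | 15.4% | 34% | 1.42 |
| Uniform, 27.5 months | 40 weeks | 16.8% | 33% | 1.42 |
| Uniform, 27.5 months | 52 weeks | 21.8% | 31% | 1.39 |
| Uniform, 24 months | 52 weeks | 25.0% | 30% | 1.38 |
| Rising, 27.5 months | 40 weeks | 29.8% | 28% | 1.35 |
| Rising, 27.5 months | 52 weeks | 37.3% | 25% | 1.31 |

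Rising accrual was worked at 27.5 months only; a shorter accrual period would give a larger share.

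**Power, for illustration.** Take a nominal 2055 woman-years per arm, uniform accrual, A = 27.5, F = 12 and the log rate ratio method.
- Off-gel time kept: RR = 0.6 × 0.782 + 0.218 = 0.687; expected events 82.2 and 56.5; SE = 0.173; power = Φ(0.375/0.173 − 1.96) = 58%.
- Both arms cut at withdrawal: 2055 × 0.782 = 1607 woman-years; expected events 64.3 and 38.6; SE = 0.204; power = Φ(0.511/0.204 − 1.96) = 71%.

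With a 40-week endpoint the two figures are 64% and 74%. The cut loses woman-years but gains power if the effect is real. The 2055 is a target that a closed arm would not reach, so only the direction of this contrast should be relied on.

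**The case against.** Keeping women who stop treatment in the analysis is ordinary intention-to-treat practice, and an SAP not shown may set a cut for the closed arm. Part of this stands: all follow-up is a legitimate estimand, and a separate cut may exist. But the article does not merely leave a gap. It states a general rule that produces the diluted result, alongside a rationale that argues against it.

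The arm closed for futility on data that predate closure, so the closure decision does not depend on off-gel time. If the true effect is near nil, dilution changes little. This stands and limits the importance of the point.

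A reader might infer that the rule hides a harm. The documents do not support that. No harm signal is reported, and the section Trial oversight gives the monitoring committee unblinded seroconversion data at every meeting. What remains is that the final reported estimate could understate a harm if one existed.

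A reader might also infer that women withdrawn at closure knew their allocation. That is plausible, since only 2% women were taken off gel, but it is not stated. Any resulting change in behaviour could bias the estimate in either direction.

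Finally, a reader might infer that placebo women enrolled after closure will be compared with the 2% arm. The article describes the 1:1 allocation but does not say they enter that comparison, so this rests on silence. Nor is attendance at the long visits only, with fewer pregnancy tests, what makes the censoring unequal; the wording of the trigger does that.

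**Conclusion.** The point holds, for the 2% versus placebo comparison only. The two sections read together assign post-closure, off-gel time to 2% gel, and they apply the pregnancy trigger unequally after closure.

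The size is an assumption-based range, because the article gives neither the accrual curve nor the date gel was withdrawn: about 15% to 25% of 2% woman-years off gel under uniform accrual over 24 to 30 months, and up to about 37% under linearly rising accrual over 27.5 months. The pull toward no effect also requires no residual gel effect and unchanged behaviour. The direction and size of any bias from the unequal pregnancy censoring cannot be derived from the documents.

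This should be settled before the 2% results are analysed, but it does not threaten the trial's remaining primary comparison, 0.5% versus placebo.

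**What to change.** Add a paragraph to the analysis section or SAP for 2% versus placebo:

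- **HIV and adverse events.** The main analysis uses women randomised 1:1:1, with follow-up in both arms cut at the calendar date of 2% gel withdrawal. State that date. Because the cut falls before later withdrawals, the unequal pregnancy trigger no longer arises.
- **Infections around the cut.** HIV is tested at weeks 12, 24, 40 and 52, so an infection acquired on gel may first be detected after the cut. Fix one rule, identical in both arms, for infections first detected at the next scheduled test.
- **Sensitivity analysis.** Report all follow-up, including post-closure off-gel time.
- **Week-24 gonorrhoea and chlamydia prevalence.** Restrict to concurrently randomised women whose week-24 visit preceded gel withdrawal.

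The cost is the loss of post-closure woman-years in this one comparison. A detection window also has a trade-off: allowing one readmits some off-gel time, and omitting it drops some infections acquired on gel. The 0.5% versus placebo analysis does not change.

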### Closure of 2% study arm

Following a review of the data accrued by 15^th ^January 2008, the IDMC recommended that the 2% gel arm should be terminated on the grounds of futility, indicating that continuation of this study arm would be unlikely to demonstrate significant benefit of this concentration of PRO 2000/5. This recommendation was accepted by the TSC, and women remaining on 2% gel at that time were withdrawn from gel, but asked to continue to attend the long clinic visits at weeks 4, 12, 24, 40 and 52.

The closure of the 2% arm provided an opportunity to redirect resources to maximise the precision and power of the trial for the 0.5% gel *vs *placebo comparison. It was decided to continue with the original enrolment targets, but with women randomised in a 1:1 ratio to the 0.5% and placebo arms.

Figure 3 shows the estimated power of the study following the above design changes, with a 52 week primary endpoint and increased enrolment to the 0.5% and placebo arms. It shows that the trial will now have 80% power to detect a lower effect size of 35% assuming a control incidence of 4% (conservative) in the control arm. This increases to 85% and 88% assuming a control incidence of 4.5% and 5% respectively.

**Figure 3 F3:**
[figure not shown]
**Effect on study power when follow-up for primary endpoint increased from 40 to 52 weeks for different assumptions concerning adherence and HIV incidence**.

### Timing of primary endpoint

The primary endpoint was initially planned to be HIV incidence up to 40 weeks follow-up. It was argued that follow-up and adherence to gel use were likely to decrease over time and that a long duration of follow-up might therefore compromise the ability of the trial to demonstrate product efficacy. Given the need for proof of concept that HIV incidence can be reduced by a topical microbicide, a short follow-up period of 6 months or even 3 months might be adopted to maximise adherence and thus estimated product efficacy. However, this has to be weighed against the cost and complexity of enrolling very large numbers of women in order to accrue sufficient woman-years of observation with such a short follow-up period. The choice of 40 weeks follow-up was a compromise designed to ensure adequate adherence and follow-up without an undue increase in cost and logistical difficulty.

During the course of the trial, after monitoring adherence and follow-up rates in May 2008, it was clear that the initial concerns justifying the adoption of a shorter follow-up were not supported by the data. There was little evidence of fall off in follow-up between weeks 40 and 52, and all study sites had achieved follow-up of over 80% of expected participants at the 52 week visit. Moreover, adherence to gel had remained high with gel use reported at more than 85% of sex acts throughout follow-up. Therefore a change of time point for the primary analysis was considered due to the advantages of longer term follow-up and increased power with the increased woman- years.

Table 2 illustrates the trade-off between increased woman-years and potentially reduced adherence (implying a smaller treatment effect) for a primary endpoint of 52 weeks instead of 40 weeks, assuming HIV incidence in the placebo arm is 4.0 per 100 woman-years, with efficacy estimates ranging from 30% to 40% with 80% gel adherence up to 40 weeks. If gel adherence remains at 80% from 40 to 52 weeks (scenario 1), study power is increased substantially with a 52 week endpoint, from 85% to 90% for 40% effect size. Even if adherence falls as low as 50% from week 40 to week 52 (scenario 2), there is still a slight increase in study power with the 52 week endpoint (85% to 86%), and only a small change in the measured efficacy (37% compared to 40%). In the unlikely worst case scenario of the adherence dropping to 0% (scenario 3) then the corresponding power drops to 79% (from 85%) and efficacy measure to 34% (from 40%).

**Table 2 T2:** Trade-off between increased woman-years (power) and falling adherence.

**Scenario**	**Week**	**Adherence**	**Observed reduction** **in HIV incidence***	**95% CI**	**% power**
1. Adherence is unchanged from Week 40 to week 52	40	80%	40%	(17%, 56%)	85%
	52	80%	40%	(20%, 55%)	90%
	40	80%	35%	(11%, 52%)	72%
	52	80%	35%	(14%, 51%)	80%
	40	80%	30%	(6%, 48%)	55%
	52	80%	30%	(8%, 47%)	64%

2. Adherence drops to 50% at week 52	40	80%	40%	(17%, 56%)	85%
	52	50%	37%	(16%, 53%)	86%
	40	80%	35%	(11%, 53%)	72%
	52	50%	33%	(12%, 49%)	75%
	40	80%	30%	(6%, 48%)	55%
	52	50%	29%	(8%, 46%)	66%

3. Adherence drops to 0% at week 52	40	80%	40%	(17%, 56%)	85%
	52	0%	34%	(14%, 50%)	79%
	40	80%	35%	(11%, 52%)	72%
	52	0%	29%	(6%, 45%)	63%
	40	80%	30%	(6%,48%)	55%
	52	0%	25%	(2%, 42%)	50%

*Compared to placebo

All figures are based on following assumptions:4% HIV incidence in control arm; 85% retention at week 40; 80% retention at week 52

Based on these observations, a proposal was made to change the primary endpoint to HIV incidence by the week 52 visit, and this decision was endorsed by the TSC. This decision was made without disclosure of the accruing data on HIV incidence in the remaining two study arms.

